### **6.3. Inclusion and exclusion criteria**

This study will be conducted in healthy children and young adults, who meet the following inclusion and exclusion criteria:

#### **6.3.1. Inclusion Criteria**

The participant must satisfy all the following criteria to be eligible for the study:

- Healthy child or adolescent aged 6-17 years (upper age limit is 17 years and 8 months so that both prime and booster are expected to take place prior to their 18th birthday)
- Able and willing (in the Investigator's opinion) to comply with all study requirements (participant's or their parents/guardians must not rely on public transport or taxis).
- Willing to allow the investigators to discuss the participant's medical history with their General Practitioner and access all medical records when relevant to study procedures.
- Parent/guardian to provide informed consent for participants under the age of 16; it will be assumed that participants aged 16 and over are able to provide consent for themselves, however parental support will be sought and investigators will reserve the right to refuse enrolment if concerns arise

#### **6.3.2. Exclusion Criteria**

The participant may not enter the study if any of the following apply:

- Child of an staff member of the Oxford Vaccine Group
- History of laboratory confirmed COVID-19 (A positive result on a validated test for SARS-CoV-2 or seropositivity for SARS-CoV-2 before enrolment)
- Chronic respiratory diseases, including mild asthma (resolved childhood asthma is allowed)
- Prior receipt of MenB vaccine
- Prior receipt of any vaccines (licensed or investigational)  $\leq 30$  days before enrolment
- Planned receipt of any vaccine other than the study intervention within 30 days before and after each study vaccination
- Prior receipt of an investigational or licensed vaccine likely to impact on interpretation of the trial data (e.g. Adenovirus vectored vaccines, any coronavirus vaccines)

- Administration of immunoglobulins and/or any blood products within the three months preceding the planned administration of the vaccine candidate
- Any confirmed or suspected immunosuppressive or immunodeficient state, including HIV infection; asplenia; recurrent severe infections and use of immunosuppressant medication within the past 6 months, except topical steroids or short-term oral steroids (course lasting <14 days)
- Any autoimmune conditions,
- History of allergic disease or reactions likely to be exacerbated by any component of the ChAdOx1 nCoV-19 or MenB vaccines
- Previous diagnosis of Kawasaki disease
- Any history of angioedema
- Any history of anaphylaxis
- Pregnancy, lactation or willingness/intention to become pregnant during the study
- Any history of cancer
- Bleeding disorder (e.g. factor deficiency, coagulopathy or platelet disorder), or prior history of significant bleeding or bruising following IM injections or venepuncture
- Any other serious chronic illness requiring hospital specialist supervision
- Congenital cardiovascular conditions
- Any other significant disease, disorder or finding which may significantly increase the risk to the participant because of participation in the study, affect the ability of the participant to participate in the study or impair interpretation of the study data.

#### 6.3.3. Re-vaccination exclusion criteria

Participants who develop COVID-19 symptoms and have a positive PCR test after the first vaccination can only receive a booster dose after a minimum 4 weeks interval from their first PCR positive test, provided their symptoms have significantly improved. The decision to proceed with booster vaccinations in those cases will be at clinical discretion of the investigators. For participants who are asymptomatic and have a positive PCR test, a minimum of 2 weeks from first PCR positivity will be required before boosting.

The following AEs associated with any vaccine, or identified on or before the day of vaccination, constitute absolute contraindications to further administration of an IMP to the participant in question. If any of these events occur during the study, the participant will be withdrawn from the study and followed up by the clinical team or their GP until resolution or stabilisation of the event:

- Anaphylactic reaction following administration of vaccine
- Pregnancy

#### 6.3.4. Effective contraception for female participants

All female participants aged 11 and over will be required to undergo urinary pregnancy testing at the V1 and booster visit. During the consent process, it will also be explained to all female participants aged 11 and over, that they are required to use contraception and avoid getting pregnant whilst enrolled in this study. To date, there have been more than 40 pregnancies declared by participants in COV001 and COV002, including data from South African and Brazilian sites. Green Book guidance reiterates that there are no immediate safety concerns arising from using adenovirus vectored vaccines in women of child-bearing age, however they are advised to postpone further immunisations should they fall pregnant during a course of immunisations and to postpone starting a schedule of immunisations until a pregnancy is completed [34].

#### 6.3.5. Withdrawal of Participants

In accordance with the principles of the current revision of the Declaration of Helsinki and any other applicable regulations, a participant or their parent/guardian has the right to withdraw from the study at any time and for any reason, and is not obliged to give his or her reasons for doing so. The Investigator may withdraw the participant at any time in the interests of the participant's health and well-being. In addition, the participant may withdraw/be withdrawn by their parents/guardian for any of the following reasons:

- Administrative decision by the Investigator.
- Ineligibility (either arising during the study or retrospectively, having been overlooked at screening).
- Significant protocol deviation.
- Participant non-compliance with study requirements.
- An AE, which requires discontinuation of the study involvement or results in inability to continue to comply with study procedures.

The reason for withdrawal will be recorded in the CRF. If withdrawal is due to an AE, appropriate follow-up visits or medical care will be arranged, with the agreement of the participant (and their parents/guardian), until the AE has resolved, stabilised or a non-trial related causality has been assigned. The DSMB or DSMB chair may recommend withdrawal of participants.

Any participant who is withdrawn from the study may be replaced, if that is possible within the specified time frame. If a participant withdraws or their parent/guardian withdraws them from the study, data and blood samples collected before their withdrawal will still be used on the analysis. Storage of blood samples will continue unless the participant or their parent/guardian specifically requests otherwise. In all cases of participant's withdrawal, long-term safety data collection, including some procedures such as safety bloods, will continue as appropriate if participants have received one or more vaccine doses, unless they (and their parents/guardian) decline any further follow-up.

If a participant wishes to withdraw from the study because of the intensity of study visits or procedures and the commitment this requires, but are willing to remain in the study, they will be offered the option to discontinue some study procedures (e.g. booster dose in 2-dose groups, blood samples, vaccine diary). This

allows continued data collection on core study data for safety, immunogenicity and efficacy outcomes. This will be facilitated by having the option of visits conducted by phone remotely, and entering this data into the CRF.

#### **6.3.6 Declining booster vaccinations**

Following the updated guidance from the MHRA and JCVI on 7th April 2021 regarding the use of ChAdOx1 nCoV-19 in under 30-year olds, it may be expected that some participants or their parents wish to decline a booster vaccination. This should be recorded in the CRF and other study procedures may continue as scheduled. It will not automatically lead to withdrawal from the study unless explicitly stated by the participant or their parent.

### **6.4. Contraception**

Female participants of childbearing potential are required to use an effective form of contraception from one month before prime until three months after boost immunisation. A participant of childbearing potential is defined as a pre-menopausal female who is capable of becoming pregnant, and for the purposes of this study all participants aged 11 and over will be asked to provide a sample for a urine pregnancy test. This will be made clear on the participant information sheets and also on the consent forms,

Acceptable forms of contraception for female volunteers include:

- Established use of oral, injected or implanted hormonal methods of contraception
- Placement of an intrauterine device (IUD) or intrauterine system (IUS)
- Total hysterectomy/Bilateral Tubal Occlusion
- Barrier methods of contraception (condom or occlusive cap with spermicide)
- Participants whom are not yet sexually active

### **6.5. Pregnancy**

Should a participant become pregnant during the trial, no further study IMP will be administered. She will be followed up for clinical safety assessment with her ongoing consent and in addition will be followed until pregnancy outcome is determined. We would not routinely perform venepuncture in a pregnant participant unless there is clinical need.

## 7. TRIAL PROCEDURES

This section describes the trial procedures for evaluating study participants and follow-up after administration of study vaccine.

### 7.1. Schedule of Attendance

All participants will have clinic attendances and procedures as indicated in the schedule of attendances. Participants will either receive the ChAdOx1 nCoV-19 vaccine or MenB, and undergo follow-up for a total of 12 months from the first vaccination visit. Additional visits or procedures may be performed at the discretion of the investigators, e.g. further medical history and physical examination, or additional blood tests and other investigations if clinically relevant.

### 7.2. Observations

Temperature will be measured at the time-points indicated in the schedule of procedures. All participants will undergo an online screening questionnaire and targeted physical examination if considered necessary prior to vaccination on D0. The purpose of this examination is to assess and document the participant's baseline health status so that any later change can be determined. Temperature will be measured at pre-enrolment at visit 1 as part of baseline schedule. Further medical history, physical examination and observations may be done throughout the study based on clinical discretion.

### 7.3. Blood tests

Safety bloods will be taken for a subset of up to 40 participants in groups 3 and 4, as outlined in tables 5b and 5d. These will include a full blood count, urea and electrolytes, liver function tests, CRP, clotting screen and D-dimer. Reference ranges will be in accordance with local NHS guidelines. Abnormalities occurring outside this range will be graded in severity and those scoring a grade 3 or above will be classified as an AE.

Immunology; Immunogenicity will be assessed by a variety of immunological assays. This may include antibodies to SARS-CoV-Spike and non-Spike antigens by ELISA, ex vivo ELISpot assays for interferon gamma and flow cytometry assays, neutralising and other functional antibody assays and B cell analyses, virus neutralising Ab (NAb) assays against live and/or pseudotype SARS-CoV-2 virus. Other exploratory immunological assays including cytokine analysis and other antibody assays, DNA analysis of genetic polymorphisms potentially relevant to vaccine immunogenicity and gene expression studies amongst others may be performed at the discretion of the Investigators. Further exploratory immunology assays may be performed at the discretion of the Investigators on HIV and non-HIV cohorts, including, but not limited to: T cell Proliferative responses to SARS-CoV-2 antigen; T cell cross-reactivity to circulating common cold coronaviruses; Multiparameter immunophenotyping by CyTOF; BCR and TCR repertoire analysis; Serum analysis by Luminex (including inflammatory, anti-inflammatory and adaptive cytokines, chemokines, growth factors and antimicrobial proteins); HIV viral reservoir; amongst others.

Collaboration with other specialist laboratories in the UK, Europe and outside of Europe for further exploratory tests may occur. This would involve the transfer of serum or plasma, PBMC and/or other study samples to these laboratories, but these would remain anonymised. Informed consent for this will be gained from participants. This would be in line with the national guidance and policy for submitting samples for testing at reference labs. Immunological assays will be conducted according to local SOPs.

Participants or their parent/guardian will be informed that there may be leftover samples of their blood (after all testing for this study is completed), and that such samples may be stored indefinitely for possible

future research (exploratory immunology), including genotypic testing of genetic polymorphisms potentially relevant to vaccine immunogenicity. Participants or their parents/guardians will be able to decide if they will permit such future use of any leftover samples. With the participant's or parent/guardian's informed consent, any leftover cells and serum/plasma will be frozen indefinitely for future analysis of COVID-19 and other coronaviruses related diseases or vaccine-related responses. If a participant or their parent/guardian elects not to permit this, all of that participant's leftover samples will be discarded after the required period of storage to meet Good Clinical Practice (GCP) and regulatory requirements. Samples that are to be stored for future research will be transferred to the OVC Biobank (REC 16/SC/0141).

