| Primary
To assess the safety, tolerability and reactogenicity profile of a prime-boost regimen (with an interval between prime and boost of 28 OR 112 days in 12-17 year olds, and interval of 112 days in 6-11 year olds) of the candidate vaccine ChAdOx1 nCoV-19 ( $5.0 \times 10^{10}$ vp / $5.0 \times 10^{10}$ vp) in children aged 6-17 years. | a) occurrence of solicited local reactogenicity signs and symptoms for 7 days following vaccination;
b) occurrence of solicited systemic reactogenicity signs and symptoms for 7 days following vaccination;
c) occurrence of unsolicited adverse events (AEs) for 28 days following vaccination;
d) occurrence of SAEs and disease enhancement episodes
e) occurrence of abnormal laboratory findings (Grade 3 and above) | a)-c) as stated, d) throughout the study, e) D2 and D7 post-boost blood tests (safety bloods) |
| Secondary
To assess cellular and humoral immunogenicity of ChAdOx1 nCoV-19 ( $5.0 \times 10^{10}$ vp / $5.0 \times 10^{10}$ vp) given as homologous prime boost (at 28 and 112 days post prime in 12-17 year olds, and 112 days post prime in children aged 6-11 years)                                                                               | a) Quantify antibodies against SARS-CoV-2 spike protein (seroconversion rates)
b) Virus neutralising antibody (NAb) assays against live and/or pseudotype SARS-CoV-2 virus
c) Interferon-gamma (IFN- $\gamma$ ) enzyme-linked immunospot (ELISpot) responses to SARS-CoV-2 spike protein
d) cell analysis by flow cytometry assays                                                                                            | Blood samples drawn at D0, D28, D56, , D84, D112, D140, D182 and 364                          |

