### 9.10. Reporting Procedures for All Adverse Events

All local and systemic AEs occurring in the 28 days following each vaccination observed by the Investigator or reported by the participant, whether or not attributed to study medication, will be recorded in electronic diaries or study database. All AEs that result in a participant's withdrawal from the study will be followed up until a satisfactory resolution occurs, or until a non-study related causality is assigned (if the participant consents to this). SAEs and Adverse Events of Special Interest (as outlined in Table 9) will be collected throughout the entire trial period.

The severity of clinical adverse events will be assessed according to scales based on FDA toxicity grading scales for healthy adolescents and children enrolled in preventive vaccine clinical trials. Severity grading criteria for temperature readings are given for adolescents. The normal ranges for a tympanic temperature in children aged 6-11 years is **35.8-38.0 C** (severity grading criteria not available).

Safety bloods will be assessed in accordance with normal ranges. Local sites will be responsible for following up any abnormal blood results the reference range which are of clinical concern. Severity grading scores are shown in Table 11, based on guidance from the Department of Aids (DAIDs) and OUH NHS Trust [37-38]

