| Biochemistry      |      |                     |                                                                      |                    |                    |                   |                   |
| Sodium            | Low  | mmol/l              | 135 - 145                                                            | 135 -146           | 147-148            | 149-150           | > 150             |
|                   | High | mmol/l              |                                                                      |                    | 132-134            | 130-131           | < 130             |
| Potassium         | Low  | mmol/l              | 3.5 - 5.0                                                            | 3.4 - 5.0          | 3.2-3.3            | 3.1               | 2.5-3.0           |
|                   | High | mmol/l              |                                                                      |                    | 5.1-5.2            | 5.3-5.4           | 5.5-6.5           |
| Urea              |      | mmol/l              | 2.5 – 6.0                                                            | 6.0-6.8            | 6.8-7.9            | 8.0-9.5           | >9.5              |
| Creatinine        |      | μmol/l              | 5-6 yrs: 25-42
7-8 yrs: 30-48
9-10 yrs: 28-57
11 yrs: 36-64 | Up to 1.1x ULN     | 1.1-1.5 x ULN      | >1.5 – 2 x ULN    | >2-3xULN          |
| Bilirubin         |      | μmol/l              | 0 -21                                                                | Up to 1.1x ULN     | 1.1 – 1.6 x ULN    | 1.6-2.6 x ULN     | >2.6xULN          |
| ALT               |      | IU/L                | 10 - 45                                                              | 1.1x ULN 45-49     | 1.1-2.5xULN 49-112 | >2-.5xULN 113-225 | >5-10xULN 226-450 |

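### Table 11 grades D-dimer as Grade 3 above 0.5 ng/ml although its own normal range is below 500 ng/ml, and this row feeds primary endpoint (e)

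*Protocol*

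**What the plan says.** Section 4 lists as primary outcome (e) "occurrence of abnormal laboratory findings (Grade 3 and above"), with time points "e) D2 and D7 post-boost blood tests (safety bloods"). Section 7.3 limits the sampling: "Safety bloods will be taken for a subset of up to 40 participants in groups 3 and 4". D-dimer is among the tests named there.

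The grading instructions stand in two places.

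- Section 7.3: "Reference ranges will be in accordance with local NHS guidelines". It continues: "Abnormalities occurring outside this range will be graded in severity and those scoring a grade 3 or above will be classified as an AE". It does not name the grading scale.
- Section 9.10: "Safety bloods will be assessed in accordance with normal ranges". It continues: "Severity grading scores are shown in Table 11, based on guidance from the Department of Aids (DAIDs) and OUH NHS Trust". It does not repeat that a value must be out of range before it is graded.

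Table 11 has its own normal-range column. In the D-dimer row the normal range is below 500 ng/ml, the cells for Grades 0, 1 and 2 are empty, and Grade 3 is above 0.5 ng/ml. Several other rows (INR, creatinine, bilirubin, ALP) are graded in multiples of the upper limit of normal (ULN). The ALT row prints multiples and absolute values together; its Grade 3 cell reads ">5-10xULN 226-450".

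**The concern.** A severity scale should not give its highest printed grade to values that the same row calls normal. The D-dimer row does so across almost the whole of its normal range. The error matters because a Grade 3 result is an adverse event under section 7.3 and an event for primary endpoint (e). The safety endpoints are descriptive, without significance tests (sections 10.1 and 10.4), so the Grade 3 count is itself the reported result. With at most 40 children contributing, one faulty row can dominate it.

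Appendix A records that clotting and D-dimer were added to the safety bloods in version 6.0, the version that responded to the April 2021 safety guidance. Readers will therefore look closely at this row.

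A smaller uncertainty lies beside it. Section 7.3 uses local ranges, while Table 11 prints one range per test (by age or sex for some), based in part on one trust's values. For rows graded in multiples of ULN, the protocol does not say whose ULN is multiplied.

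**Working it through.** **Inputs.** D-dimer upper limit of normal 500 ng/ml and Grade 3 limit 0.5 ng/ml (Table 11); children with safety bloods up to 40 (section 7.3; 20 in each of Tables 5c and 5d); one boost-day and one post-boost sample per child (section 7.4.3); ALT normal range 10 to 45 IU/L (Table 11). The protocol gives no expected count for endpoint (e), so there is no stated figure to reproduce.

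**1. Size of the contradiction.** 500 / 0.5 = 1,000. Both cells are in ng/ml. If the Grade 3 figure was meant in micrograms per ml, it would be 0.5 × 1,000 = 500 ng/ml, exactly the upper limit of normal. A unit slip is therefore a plausible cause, though the protocol does not confirm it.

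**2. Table 11 applied alone.** A child is Grade 3 if D-dimer exceeds 0.5 ng/ml. The protocol gives no D-dimer distribution, so one is assumed here: lognormal, median 50 to 400 ng/ml, geometric standard deviation 1.5 to 3. The lowest probability of exceeding 0.5 ng/ml over these settings is 0.999986, and 40 × 0.999986 rounds to 40.0. In practice every sampled child is Grade 3.

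**3. Section 7.3 condition applied first, or the limit corrected to 500 ng/ml.** Only values above the range are graded. With Grades 1 and 2 empty, each such value goes directly to Grade 3. The number depends on the share of children above the limit, which the protocol does not give. For illustration only:

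| Assumed share above the limit | Expected of 40 | Chance of at least one |
|---|---|---|
| 1% | 0.4 | 1 − 0.99^40 = 33.1% |
| 5% | 2.0 | 1 − 0.95^40 = 87.1% |
| 10% | 4.0 | 1 − 0.90^40 = 98.5% |

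Under the lognormal settings of step 2, the share above 500 ng/ml runs from 0% to 42%, or 0 to about 17 of 40. The table therefore shows how the count behaves; it does not predict it.

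**4. ALT row.** With ULN 45: 45 × 1.1 = 49.5, 45 × 2.5 = 112.5, 45 × 5 = 225 and 45 × 10 = 450. These match the printed absolute limits of 49, 112/113, 225/226 and 450. The row's two scales agree at ULN 45 and at no other value.

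**5. Amount to regrade.** 40 children × 2 samples = at most 80 D-dimer results.

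**The case against.** The strongest defence is section 7.3 itself. It grades only values outside the reference range, so a D-dimer between 0.5 and 500 ng/ml would normally never be graded. Section 9.10 also starts from normal ranges. This stands to a large degree: the 40-of-40 result arises only if Table 11 is used without that condition. It does not repair the row. Section 9.10 sends the grader to Table 11 without repeating the condition, section 7.3 does not name Table 11, and the printed limit is wrong on any reading. A lost micro sign is an unlikely explanation, because the creatinine and bilirubin rows print theirs.

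A reader might infer more than the documents support.

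- **That local ranges and Table 11 contradict each other outright.** They can be read as consecutive steps: the local range decides what is abnormal and Table 11 supplies the grade. What remains open is whose ULN applies.
- **That ALT will be graded differently between sites.** This needs local ULNs other than 45, and the protocol gives none.
- **That a real signal after the boost would be lost.** Sampled children also have safety bloods on the day of the booster (section 7.4.3), so an artefact of the limit would show there too. It would be confined to D-dimer, and blood results are kept as source data (section 11.3), so regrading is possible.
- **That vaccination would be halted by it.** The percentage holding rules in section 9.17.1 need onset within 2 days and persistence at Grade 3 beyond 72 hours. A single Grade 3 D-dimer does not meet them.

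Treating any raised D-dimer as Grade 3 may be a deliberate choice by the sponsor. If so, the protocol should say so.

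**Conclusion.** The point holds for the D-dimer row. Its Grade 3 limit lies 1,000-fold below the row's own upper limit of normal, and it feeds a primary endpoint and the definition of an adverse event. That rests on the printed figures alone.

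The effect on the count depends on the reading. Table 11 taken literally and alone makes practically all of up to 40 children Grade 3; this assumes only that healthy children's values exceed one thousandth of the normal limit. With the section 7.3 condition, or a corrected unit, the count is the number above the range, all of them Grade 3 for want of a lower grade. It is tempting to describe endpoint (e) as running from a few percent to everyone, but the documents do not support the lower figure: it rests on an assumed rate.

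The missing statement on local or printed ULN is a clarification of second rank. The row should be corrected before endpoint (e) is tabulated.

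**What to change.** 1. Reconcile section 7.3, section 9.10 and Table 11 by correcting the D-dimer row, so that its units agree and Grade 3 cannot include values inside the stated normal range. The sponsor sets the limit; none is proposed here. If every raised value is meant to be Grade 3, state that this is intended.
2. Say in section 9.10, as section 7.3 already does, that only values outside the reference range are graded, and name Table 11 in section 7.3 as the scale.
3. State whether the local or the printed ULN applies to rows graded in multiples of ULN, including ALT, where both forms are printed.
4. Regrade any D-dimer results already entered.

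The cost is one table row, a few sentences and the regrading of at most about 80 results. No new data are needed. The only drawback is that a Grade 3 count already reported may change. Central grading at all sites, or taking D-dimer out of the Grade 3 count, would go further than the contradiction requires.
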